#### Adverse events

2.3.10

At each visit, the investigator will evaluate the patient to determine whether any adverse events (AEs) have occurred. AEs may be directly observed, reported spontaneously by the patient, or questioned by a study team member patient at each study visit in the clinic or on the telephone. The NCI Common Terminology Criteria for Adverse Events version 4 (NCI CTCAE v4.03) will be used to classify and grade the intensity of adverse events during and after treatment. A serious adverse event (SAE) or AE is defined as the diagnosis or a sign or symptom as applicable as per the CTCAEv4.03. All events, whether related or not, will be recorded and graded and the worst toxicity will be recorded. All laboratory values will be evaluated by the investigator as to their clinical significance. All abnormal laboratory values considered clinically significant by the investigator will be recorded as an AE.

All AEs/SAEs will be followed up till resolution or stabilization. In case of unresolved AEs, including significant abnormal laboratory values at the end of treatment assessment, these events will be followed up until resolution or until they become clinically not relevant. Pre-planned procedures or hospitalization for pre-existing conditions that do not worsen in severity will not be reported as SAEs. Progressive disease or death due to progressive disease will not be reported as an SAE. AEs/SAEs occurring after the end of the study period will not be reported.

The definitions of AEs/SAEs and reporting are outlined in **Appendix 2** in **Supplementary Material**.

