### Study design

2.1

The study is a prospective, randomized, open-label phase II/III study.

For the phase II part of the study, eligible patients will be randomized 1:1 to the statin + NACTRT arm or the only NACTRT (standard) arm. The statin arm will receive rosuvastatin 20 mg for 12–16 weeks. Pathological response would be assessed following surgery.

A follow-on phase III trial with 3-year DFS as the endpoint will be planned depending on how the statin arm fares in terms of feasibility, safety, and efficacy.

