#### Screening

2.3.1

All patients diagnosed as having rectal cancer will undergo a standard staging workup that includes but may not be limited to a colonoscopy, biopsy, pelvis MRI, and contrast-enhanced computed tomography (CECT) of the thorax and abdomen, carcino embryonic antigen (CEA), complete blood count and biochemistry tests [random blood sugar (RBS), liver function test (LFT), and renal function test (RFT)]. This is part of the standard care. Treatment decisions are taken by a multi-disciplinary tumor board (MDTB). Previously untreated rectal cancer patients who are planned for NACTRT will be screened for the study and an anonymized screening log will be maintained.

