#### Enrolment in the study/consent

2.3.2

All patients eligible for study participation who satisfy the inclusion/exclusion criteria (**Table 2**, **Appendix 4** in **Supplementary Material**) will be enrolled after an informed consent form (ICF), provided by a study team member, is signed. An enrolment log will be maintained and a study ID will be allocated to each patient at study entry.

**Table 2 T3:** Inclusion and exclusion criteria.

Inclusion criteria	Exclusion criteria
•Age between 18–70 years •Subjects willing to sign the informed consent •Eastern Cooperative Oncology Group (ECOG) performance status 0 to 2 •Histologic diagnosis of rectal adenocarcinoma •Clinical and radiological T2–4 (any) N (any) M0 •Fit to receive neoadjuvant chemoradiotherapy •Absence of colorectal synchronous primary •No prior rectal cancer treatment received	•Patients with proven metastatic disease •History of Crohn's disease or ulcerative colitis •Inherited polyposis syndromes •Ongoing statin or aspirin therapy for cardiovascular disease •Pregnant or nursing women •Subject not willing to provide informed consent •Comorbidities precluding statins and neo-adjuvant therapy including but not limited to Hepatitis **, *acute or chronic kidney disease* •Prior anti-neoplastic therapy •Patients already taking the following drugs: cyclosporine, gemfibrozil, atazanavir/ritonavir, lopinavir/ritonavir, tipranavir/ritonavir or simeprevir, eltrombopag, dronedarone, itraconazole, fluconazole or ketoconazole; coumarin anticoagulants; lipid-lowering therapies: fibrates or lipid-modifying doses (greater than or equal to 1g/day) of niacin; aluminum and magnesium hydroxide combination; antacid; and erythromycin. *Hepatitis will be defined as sustained elevation of transaminases (two readings 5–7 days apart) ≥3X upper limit of normal. *Kidney disease will be defined as elevated creatinine levels above the upper limit of normal

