#### Assessment of response

2.3.6

Clinical and radiological assessment will be done at 6–8 weeks after completion of NACTRT. Eligible patients will undergo standard surgery (anterior resection, abdominoperineal resection, inter-sphincteric resection, or multi-visceral resection) according to the level and extent of growth. If the reassessment MRI at 12–14 weeks after completion of NACTRT shows inoperable disease, then the patient will be deemed a non-responder and analyzed as part of the non-pCR group. These patients, if on the rosuvastatin arm, will stop the statin on the day they are deemed inoperable by the MDTB. These patients will receive further chemotherapy to downstage the disease as per the current standard of care. A histopathological examination will be conducted for the patients operated on and the pathological response rate and tumor regression grade (TRG) will be judged according to the American Joint Committee on Cancer (AJCC) (**Appendix 1** in **Supplementary Material**). A pCR is defined as no residual cancer found on histological examination of the TME specimen (Grade 0 AJCC or Grade 1 Mandard’s). The pathologist assessing the specimen will be blinded to the treatment that the patient received.

Following surgery and the availability of the histopathology report, the patient would have completed the active phase of the study and will be followed up according to standard follow-up protocol. Survival details will be collected at each follow-up visit or telephonically if the patient misses a visit for any reason.

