#### Study specific investigations

2.3.8

All investigations will be done as per the current standard of care. There will be no additional planned blood tests or imaging done for the purpose of the study. In patients who agree to participate in the molecular sub-study, the baseline samples will be taken at the time of the baseline endoscopy and post-treatment samples for the operated patients will be from the resected specimen. Post-treatment samples for patients who are not operated on (approximately 30% of those receiving NACTRT) will be collected by conducting a repeat limited sigmoidoscopy. The patients will be reimbursed for this and the same is mentioned in the ICF as well. The follow-up will be as per the prevailing standard of care.

The schedule of events are depicted in **Table 3**.

**Table 3 T4:** Schedule of events.

	Baseline	Randomization	Week 2 visit ±3 days	Week 4 visit ± 3days	Week 6 and 7 visit ±3 days	Week 12 visit ±3 Days	Week 14 to 16 visit ±3 days
Informed Consent	✓						
Screening of patients with biopsy-confirmed adenocarcinoma of the rectum	✓						
Collection of four additional tissue samples for molecular sub-study	✓						
Collection of 7–8 ml of blood	✓						
Randomization		✓					
Both arms NACTRT			✓	✓	✓		
Statin dispensed		✓			✓		**
Statin pill counts			✓	✓	✓		✓
Adverse event/serious adverse event reporting			✓	✓	✓	✓	✓
Clinical review			✓	✓	✓	✓	✓
Radiological review						✓*	✓*
MDTB decision for surgery							✓
Collection of four additional tissue sample post-surgery							✓#

*Radiological assessment will be done at 6–8 weeks after completion of NACTRT.

**Rosuvastatin will be stopped a day prior to surgery (operable patients) or on the day deemed inoperable (inoperable patients).

#Paired tissue samples will be collected from patients who are operated on via the resected specimen (post-treatment sample) or fresh biopsies for patients who are not operated on.

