### Statistical consideration

2.5

A) The primary efficacy variable is a pathological complete response which is defined as the absence of microscopic tumors in the resected specimens in patients who undergo surgery following neoadjuvant chemoradiotherapy.

B) The secondary efficacy variables are toxicity and 3-year DFS.

C) Toxicity will be assessed as detailed below. The NCI Common Terminology Criteria for Adverse Events version 4 (NCI CTCAE v4.03) will be used to classify and grade the intensity of adverse events during and after chemo-radiotherapy. The worst grade of each toxicity episode will be recorded. All events regardless of attribution will be graded so as to ensure objectivity in reporting as per accepted international guidelines. The details will be entered in the dataset.

D) Any adverse event that occurs from the day of randomization until the end of study visit will be defined as an acute adverse event. Events that occur thereafter will be defined as chronic adverse events. Both acute and chronic adverse events will be recorded however only events happening till 30 days after surgery will be reported and not beyond.

E) Postoperative morbidity and mortality will be any event occurring from the day of surgery until 30 days.

F) Disease-free survival is defined as the time from the date of randomization until the date of disease recurrence or until death from any cause.

G) Progression-free survival (PFS) is defined as the time from the date of randomization until the date of disease recurrence or until death from any cause. If there is a clinical suspicion of progression, further workup and management will be as per the institutional standard. Progression will be assessed by the investigator using appropriate workup and investigations, as per routine care.

H) Overall survival is defined as the time from the date of randomization until the date of death from any cause.

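### In this open-label trial a laboratory abnormality becomes an adverse event through the unblinded investigator's view of its clinical significance, so the between-arm comparison of laboratory toxicity is open to differential recording

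*Protocol article*

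**What the plan says.** **Recording rule.** Section 2.3.10 (Adverse events) gives the judgement to the investigator: "All laboratory values will be evaluated by the investigator as to their clinical significance". It continues: "All abnormal laboratory values considered clinically significant by the investigator will be recorded as an AE". The visible text attaches no numeric threshold to this step. The same section adopts CTCAE v4.03 for classifying and grading events, and says that events are recorded and graded whether or not they are related to treatment.

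**Blinding.** Section 2.1: "The study is a prospective, randomized, open-label phase II/III study". The one blinded role named is in section 2.3.6 and concerns the response endpoint: "The pathologist assessing the specimen will be blinded to the treatment that the patient received".

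**Blood tests.** Section 2.3.8: "There will be no additional planned blood tests or imaging done for the purpose of the study". Investigations follow standard of care. Liver and renal function tests are named in the screening workup (section 2.3.1).

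**Entry limits.** Table 2 defines liver disease by number: "Hepatitis will be defined as sustained elevation of transaminases (two readings 5–7 days apart) ≥3X upper limit of normal". It defines kidney disease as creatinine above the upper limit of normal.

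**Use of the data.** Comparing the frequency and severity of adverse events between arms is a secondary objective (section 1.3). Toxicity is listed as a secondary variable in section 2.5 B. Section 2.1 makes the follow-on phase III trial depend on feasibility, safety and efficacy. Section 2.5 C sets the aim: "All events regardless of attribution will be graded so as to ensure objectivity in reporting as per accepted international guidelines".

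**The concern.** Grading regardless of attribution works only on what has already been accepted as an event. For laboratory values, acceptance comes earlier, through a judgement of clinical significance by someone who knows which patients take the statin. The same transaminase value could be recorded in one arm and passed over in the other.

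A second source of imbalance lies upstream. Section 2.3.5 reviews rosuvastatin patients every 2 weeks during chemoradiation and control patients according to standard practice, with no interval given. If testing follows review, the chance that an abnormality is found at all may also differ by arm.

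At stake is the laboratory part of the safety comparison. A difference could appear where none exists, or a real one could be reduced, hidden or reversed, and safety is one of the three grounds for going on to phase III.

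**Working it through.** The plan states no figure on this point, so there is none to reproduce. The check has two parts.

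**1. Passages side by side**

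- Who decides that a laboratory value is an event: the investigator (2.3.10).
- Whether that person knows the arm: yes, since the design is open-label (2.1) and only the pathologist is blinded (2.3.6).
- Which results are available to judge: those produced by standard of care (2.3.8). Their content and timing during treatment are not fixed in the article.
- What 2.5 C removes: selection by presumed cause. It does not deal with selection by clinical significance, which is a different question.

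Both rules can be followed at once, so they do not contradict each other. Following both still leaves the unblinded selection step in place.

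**2. How large the effect could be (all inputs assumed)**

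Let p be the true proportion of patients with a gradable transaminase or creatinine abnormality, and r the probability that such an abnormality is tested for and recorded. Then:

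observed rate = p × r

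observed risk ratio = true risk ratio × (r on rosuvastatin ÷ r on control)

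With equal true rates in the two arms:

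| True rate, both arms | r rosuvastatin | r control | Observed | Observed risk ratio |
|---|---|---|---|---|
| 20% | 0.80 | 0.50 | 16% v 10% | 1.60 |
| 5% | 0.90 | 0.60 | 4.5% v 3.0% | 1.50 |
| 10% | 0.90 | 0.60 | 9% v 6% | 1.50 |
| 20% | 0.90 | 0.60 | 18% v 12% | 1.50 |
| 20% | 0.60 | 0.90 | 12% v 18% | 0.67 |
| 20% | 0.80 | 0.80 | 16% v 16% | 1.00 |

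First row: 0.20 × 0.80 = 0.16 and 0.20 × 0.50 = 0.10, an apparent difference of 6 points with no true effect. With 158 patients per arm that is about 25 v 16 patients (158 × 0.16 = 25.3; 158 × 0.10 = 15.8).

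For masking, reverse the first row: r = 0.50 on rosuvastatin and 0.80 on control, with a true control rate of 20%. Control shows 0.20 × 0.80 = 16%. Rosuvastatin also shows 16% when its true rate is 0.16 ÷ 0.50 = 32%. The excess exactly hidden is 32% − 20% = 12 points. A smaller true excess would be reversed: 26% would show as 0.26 × 0.50 = 13%, below the 16% on control.

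The last row of the table shows that equal recording leaves the risk ratio undistorted. The problem is unequal recording, not under-recording as such.

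**The case against.** The strongest reply is that a clinical-significance filter is common practice, is worded identically for both arms, and sits in a condensed article. Adverse-event definitions are in Appendix 2 and drug toxicity is in Appendix 3. Neither is shown, and either may contain numeric rules. Section 2.3.10 also defines events by reference to CTCAE v4.03, which could be read as already covering graded laboratory values. Much of this stands, and it limits how strongly the point can be put. It does not remove the point: the rule that is printed routes laboratory values through the investigator's judgement, and in an open-label trial identical wording does not ensure identical application.

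Four stronger readings are tempting, and the documents do not support them.

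- *Section 2.3.10 contradicts 2.5 C.* It does not: one concerns clinical significance and the other attribution.
- *A value could be left out because it is blamed on capecitabine.* Both sections rule this out, since relatedness does not decide whether an event is recorded and graded.
- *There are no safety bloods.* The text says only that none are added to standard of care. The absence of a laboratory row in Table 3 proves little, because the table also omits the baseline liver and renal tests that section 2.3.1 says are done.
- *The entry limits in Table 2 ought to have governed follow-up.* They show that the plan can define these abnormalities by number. They were not written as toxicity criteria.

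**Conclusion.** The point holds as a weakness in how laboratory toxicity is ascertained. Recording depends on an unblinded judgement applied to results whose timing is not fixed in the article, so the between-arm comparison can be distorted in either direction and does not reach the objectivity that 2.5 C aims for.

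The size is unknown. The 16% v 10% figure and the risk ratios from 0.67 to 1.60 are illustrations resting on assumed recording probabilities. They do not show that bias is present or likely. The conclusion also assumes that the appendices not shown contain no numeric rule that overrides the printed one. The primary endpoint is not affected, because it is read by a blinded pathologist. The change is worth making because it is cheap and safety feeds the phase III decision.

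**What to change.** In section 2.3.10, for both arms:

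- Enter in the case record form every transaminase and creatinine result obtained in routine care from randomization to the end-of-study visit.
- Assign the CTCAE v4.03 grade from the number, whatever the judged significance. This takes CTCAE v4.03 to grade these tests on numeric limits, which the article does not reproduce.
- Report the worst grade by arm together with the number of patients tested and the number of tests per patient. Compare the arms within common visit windows, such as those in Table 3. More frequent testing raises the chance of a high worst grade, so a count of patients ever tested would not be enough.
- Do not compare CK grades between arms. The guidance cited under Limitations recommends CK monitoring only for symptomatic patients, so CK results would be selected by symptoms.
- Keep the investigator's judgement for relatedness and seriousness.

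This does not equalize testing between arms. It makes unequal testing visible and removes the unblinded selection at the recording step. The cost is extra data entry from existing hospital results, a grading table, and somewhat higher reported laboratory event rates in both arms. It needs no extra blood tests and leaves clinical management unchanged.

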### Study hypothesis and objective(s) in the phase II part

1.3

Hypothesis:

The addition of rosuvastatin to NACTRT will improve the pCR rate by 10% (from 15% to 25%).

Primary objective:

To determine the impact of rosuvastatin in improving pCR in patients with locally advanced rectal cancer undergoing NACTRT.

Secondary objectives:

To compare the frequency and severity of adverse events in the two arms.To compare post-operative morbidity and mortality in the two arms.To identify other potential prognostic and predictive factors determining outcomes.To compare the DFS in the two arms.To compare the OS in the two arms.Evaluate expression and localization of SATB1 and SATB2 across paired human colon/rectum and tumor samples.Correlation of expression of SATB1 and SATB2 across different grades and stages of tumor samples towards understanding CRC progression.Understand the role of SATB proteins in tumor regeneration and disease relapse by validation of the association of its expression across differentiated and undifferentiated tumors.Correlation of expression of SATB proteins across colorectal cancer subtypes-classical adenocarcinoma, mucinous adenocarcinoma, and signet ring pathology tumors.

If the phase 2 study has positive results, we plan to proceed to a phase 3 study.

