#### Follow-up procedures

2.3.5

After commencing the statin, the patients in the intervention arm will be reviewed every 2 weeks on NACRT (at 2 weeks ± 3 days, 4 weeks ± 3 days, and 6 weeks ± 3 days) either in person in the clinic or telephonically if they cannot come to the clinic due to unavoidable circumstances. Patients in the standard arm on NACTRT will be reviewed as per standard protocol. Patients in both arms will be reviewed at 6 ± 2 weeks after completion of NACTRT (weeks 12–14). At this visit, all patients will undergo restaging as per routine practice and will be evaluated by the MDTB for surgery by week 14 (± 2 weeks). Patients in both arms will be operated on if deemed to have operable disease.

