#### End of study visit

2.3.7

Patients will receive rosuvastatin for 12–16 weeks, with the treatment being discontinued 1 day prior to surgery for operable patients. The final study visit for these patients will coincide with their MDTB appointment, where the final surgical histopathology report (approximately 10–14 days post-surgery) will be reviewed. For patients deemed inoperable, the study will conclude on the day the decision of inoperability is made. At this visit, a final safety follow-up and pill count will be conducted. Following this, there will be no further active intervention, and patients will be monitored for survival. No protocol-mandated imaging or re-evaluation is planned; patients will be followed according to standard surveillance guidelines for rectal cancer patients who have undergone multimodality treatment.

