### Statistical analysis

2.6

Quantitative data will be presented as mean ± SD and categorical variables as frequencies within each cohort. The comparison of the statin and non-statin groups will be done using Fisher’s exact test or a χ2 test for categorical variables, and a Wilcoxon rank sum test for quantitative variables. Univariate analysis of significant predictors of an AJCC grade 0 response to NACTRT will be performed by a χ2 or Fisher’s exact test for categorical variables and logistic regression for quantitative variables. Multivariate analysis of statin use as a predictor of AJCC grade 0 responses to NACTRT will be done using multivariable logistic regression models. A Kaplan–Meier survival analysis will be used to determine the effect of statin use and AJCC TRG score on overall survival and disease-free survival. Cox proportional hazard models will be used to determine whether statin use was a significant predictor of recurrence and survival outcomes after adjusting for predicted covariates. All secondary endpoint comparisons will be made using the two-sided log-rank test with a 0.05 significance level. Assuming that OS demonstrates significance in the phase II study, the same criteria would be used for the analysis of PFS. For potential prognostic and predictive factors, multivariate analysis would be performed based on gender, metastasis occurrence from accrual to follow-up timepoint, histology subtype (diffuse, intestinal), and measurable disease (yes, no).

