### Rosuvastatin administration

3.2

A member of the study team will prescribe the drug and give instructions about its usage. Regular intake of the drug will be confirmed by weekly telephonic calls with the study coordinator. Patients will be followed up at regular intervals according to the study protocol unless any adverse events occur, which will be managed immediately. Drug compliance will be monitored and noted in the CRF.

The details of rosuvastatin drug toxicity, dose modification, possible drug interactions, concomitant therapy in the study, and dosing delays/dose modifications are mentioned in **Appendix 3** in **Supplementary Material**.

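### The safety rules conflict on when adverse-event reporting stops, on whether both arms share one review schedule, and on which test applies

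*Protocol article*

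**What the plan says.** Safety is a formal between-arm comparison. One phase II secondary objective (section 1.3) reads "To compare the frequency and severity of adverse events in the two arms"; another compares post-operative morbidity and mortality. Section 2.1 makes safety one of the inputs to the phase III decision, and describes the trial thus: "The study is a prospective, randomized, open-label phase II/III study".

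**Cut-off.** Section 2.3.10 states "AEs/SAEs occurring after the end of the study period will not be reported". Section 2.3.7 ties the final visit of operated patients to the tumor board appointment "where the final surgical histopathology report (approximately 10–14 days post-surgery) will be reviewed"; for inoperable patients the study ends on the day of that decision. Section 2.5 D calls events up to the end-of-study visit acute and later ones chronic, says both kinds are recorded, and adds that "only events happening till 30 days after surgery will be reported and not beyond". Section 2.5 E counts post-operative morbidity and mortality from the day of surgery to day 30.

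**Review schedule.** Section 2.3.5 sets reviews at weeks 2, 4 and 6 for the intervention arm, in clinic or by telephone. For controls it says "Patients in the standard arm on NACTRT will be reviewed as per standard protocol". Section 3.2 adds, for the study drug, "Regular intake of the drug will be confirmed by weekly telephonic calls with the study coordinator". Table 3 ticks adverse-event reporting and clinical review at weeks 2, 4, 6–7, 12 and 14–16 without separating the arms.

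**Test.** Section 2.6 states "All secondary endpoint comparisons will be made using the two-sided log-rank test with a 0.05 significance level". Earlier in the same section, categorical variables are to be compared between the groups by Fisher's exact or χ² test.

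**The concern.** Three things are at stake.

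- **Completeness.** Two sections give different end dates for the same reporting. A site that follows 2.3.10 could stop part-way through the 30-day window that defines a secondary endpoint, and late complications and deaths would be missing from it.
- **Comparability.** Section 2.3.10 detects events by observation, spontaneous report or questioning at clinic or telephone visits, so the number found depends partly on the number of contacts. Treatment is open-label, and blinding is stated only for the pathologist (2.3.6). If one arm has protocol-fixed reviews plus calls about tablet intake and the other has whatever local routine provides, a difference in event frequency may partly reflect how often patients were asked.
- **Analysis.** Read literally, the log-rank sentence covers toxicity, which 2.5 B lists as a secondary variable. The log-rank test compares times to an event. It does not compare worst grades, or the proportions with an event by day 30.

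**Working it through.** No sample-size or power figure is involved. The check sets the sections side by side and does date arithmetic.

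**1. Post-operative days at risk of being unreported**

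Inputs: window of 30 days (2.5 D–E); final visit at about day 10–14 after surgery (2.3.7). Days not covered = 30 − day of final visit.

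| Final visit | Days not covered | Share of window |
|---|---|---|
| Day 10 | 30 − 10 = 20 | 20/30 = 67% |
| Day 14 | 30 − 14 = 16 | 16/30 = 53% |
| Rule in 2.5 D followed | 0 | 0% |

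The first two rows assume that the study period in 2.3.10 ends at the final visit. Section 2.3.10 does not define the term. Section 2.3.7 supports that reading by saying when the study concludes for inoperable patients.

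**2. Whether the schedule supports the 30-day rule**

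Statin treatment runs 12–16 weeks until surgery (2.3.4.2). Counting from the start of treatment, surgery then falls at about day 12 × 7 = 84 to 16 × 7 = 112, and post-operative day 30 at day 84 + 30 = 114 to 112 + 30 = 142. Table 3's last visit window closes at 16 weeks + 3 days = day 115. Only surgery at the very start of the range would have its day 30 inside a scheduled visit; surgery at week 16 has it 142 − 115 = 27 days later. Table 3 has no day-30 column.

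**3. Patients not operated on**

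Section 2.3.8 puts these at about 30% of those receiving chemoradiation, consistent with the roughly 70% undergoing surgery in 2.4. If that held among the 316 randomized, 0.30 × 316 ≈ 95 patients would have no date from which 30 days could run. For inoperable patients, the only other stop is the day of the decision. Responders who are not operated on (2.3.9) fit neither end-of-study rule in 2.3.7.

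**4. Contacts by arm during chemoradiation, as written**

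| Source | Statin | Control |
|---|---|---|
| 2.3.5 | 3 fixed reviews (weeks 2, 4, 6) | frequency not given |
| 3.2 | weekly intake calls; 12–16 if made throughout dosing (assumption) | none applicable |
| Table 3 | weeks 2, 4, 6–7 | same columns, no split |

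The calls would extend beyond chemoradiation if made throughout dosing. After chemoradiation both arms share the week 12–14 review (2.3.5). So 2.3.5 and Table 3 disagree about controls, and the difference in control contact cannot be computed from the document.

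**5. Tests**

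Adverse-event grade and 30-day morbidity are categorical. The Fisher/χ² sentence in 2.6 covers them; the later log-rank sentence also covers them by its wording. Both cannot be the rule.

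**The case against.** On the cut-off, the best reply is that 2.5 D deals expressly with events after the end-of-study visit and reports them to day 30. If the study period in 2.3.10 is read as ending on day 30, nothing is lost for operated patients. Section 2.3.10 also refers to Appendix 2 for reporting rules, and that appendix is not shown. This much stands: a reader might infer that reporting definitely ends about two weeks after surgery, and the document does not establish that. The cut-off is also the same in both arms, so it creates no asymmetry by itself. What remains is that the main text gives two rules, and neither a day-30 contact nor an anchor for unoperated patients appears in it.

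On the schedule, a visit frequency that is not stated is not thereby lower. Controls attend for 5–6 weeks of radiotherapy, and Table 3 reads as common to both arms. The weekly calls are described as checks on intake, not as safety reviews. A reader might infer three extra safety reviews and 12–16 extra safety contacts on statin; the document shows neither. Events volunteered on a call would still count under 2.3.10, so some imbalance remains possible. Its likely direction is against rosuvastatin, which makes a low-risk conclusion harder to reach, not easier.

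On the test, 2.6 already names a suitable method, and finer detail may sit in an analysis plan that is not shown. That does not rescue a sentence which, as written, assigns the wrong test to some endpoints.

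**Conclusion.** The point holds as a set of contradictions to be reconciled, not as proof that follow-up is truncated or that controls are under-observed.

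- **Cut-off:** up to 16–20 of 30 post-operative days (53–67%) would go unreported if 2.3.10 governs and the study period ends at the visit described in 2.3.7; none for operated patients if 2.5 D governs. The missing anchor for unoperated patients, roughly 95 of 316 on the hospital's own 30% figure, exists under the 30-day rule itself.
- **Ascertainment:** 2.3.5 and Table 3 conflict. The bias, if any, probably inflates adverse-event counts on statin. Its size cannot be estimated without the control visit schedule.
- **Test:** the log-rank sentence is wrong as worded for adverse events and 30-day morbidity, and conflicts with 2.6 itself.

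The primary endpoint is untouched. The safety comparison, which informs the phase III decision and any claim that the intervention is low-risk, is affected, so the text should be amended.

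**What to change.** 1. State one adverse-event and serious-adverse-event cut-off, identically in 2.3.7, 2.3.10 and 2.5 D–E, that covers the 30-day post-operative endpoint. Define the study period. Name the anchor date for every patient not operated on, including responders without surgery; it must exist in both arms, so a last-statin-dose date alone would not serve controls. Add a day-30 collection point to Table 3.
2. State in 2.3.5 that the Table 3 adverse-event schedule applies to both arms with the same checklist. Base the between-arm comparison on events collected at those common visits, and flag events raised only in adherence calls so that they can be reported separately.
3. Limit the log-rank sentence in 2.6 to time-to-event endpoints (DFS/PFS and OS). Compare adverse events and 30-day morbidity and mortality by χ² or Fisher's exact test, with a risk difference and confidence interval.

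The cost is amendment wording, a checklist at control visits, and one brief day-30 contact or record check per patient.
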